### Data analysis

The data analysis will be done using SPSS software ver. 16 by descriptive, and inferential statistics including paired t-test, repeated measure ANOVA, Chi-squared test, Fishers exact test, ANOVA, Wilcoxon test, and Mann–Whitney test.

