### The implementation method

Based on the opinion of expert panel, a part of the strategies and goals will be determined in the form of an intervention program. After approving the protocol of the study with Ethics Committee, and obtaining the necessary coordination between the authorities of healthcare centers and hospitals, the researcher will implement the designed interventional program. After explaining the aim of the study (by [name]), verbal, and informed consent will be given from the eligible women, and if they agree, they will enter the study and be randomly divided into two groups. For sampling, eligible women will be entered into the study using the convenience sampling method. Then, for randomized assignment, the women will randomly assign either to the trial or control groups based on the table of random numbers that will be generated by Random Allocation Software 2.0. To prevent selection bias, allocation concealment to the trial or control group will be done by a researcher who does not participate in the data collection ([name]).

At first, in the 36th week of pregnancy, a pre-test will be taken from both groups and the average self-efficacy scores will be compared between the two groups. The intervention group received the self-efficacy promotion program and the control group did not receive any intervention. After delivery, their self-efficacy score will be checked between two groups. The type of intervention (e.g., role playing, peer education, home visit, virtual training, and etc.), the time of the program implementation (pregnancy, after childbirth, etc.), the people involved in the program will be determined based on the opinion of the expert panel.

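### The list of tests mixes within-arm and between-arm methods without naming the one that answers the objective, and none uses the pre-test as a covariate, which costs precision but not validity

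*Protocol article*

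**What the plan says.** The fourth-phase objective is to determine the program's effect on the self-efficacy score of teen mothers. Under The implementation method, allocation is random ("the women will randomly assign either to the trial or control groups") and the comparator is untreated ("the control group did not receive any intervention"). Scores are taken before and after delivery. At week 36, "a pre-test will be taken from both groups and the average self-efficacy scores will be compared between the two groups"; later, "After delivery, their self-efficacy score will be checked between two groups".

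Data analysis is one sentence. It promises descriptive statistics and, as inferential methods, "paired t-test, repeated measure ANOVA, Chi-squared test, Fishers exact test, ANOVA, Wilcoxon test", followed by the Mann–Whitney test. It does not tie any test to the objective, and it names no model in which the pre-test is a covariate. The sample size is left to a pilot study (Sampling method, and sample size).

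**The concern.** The listed tests answer different questions. A paired t-test on pre- and post-delivery scores asks whether one arm changed. A between-arm test asks whether the program made a difference, and only that is the objective. With no test named, the analyst may choose after seeing the data, and a within-arm result could be reported as if it were the effect.

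The pre-test is also collected from every woman but is not used in the most efficient way. ANOVA or Mann–Whitney on the post-delivery score ignores it. The group-by-time term of a repeated-measures ANOVA with one score before and one after delivery is the change-score test. That test uses the pre-test but subtracts it in full, which adds noise when the two scores are weakly correlated. Because the sample size is still to be set from a pilot, the choice of analysis bears directly on how many women are needed.

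**Working it through.** The article states no sample size, significance level, power, SD or correlation, so there is no figure to reproduce. Everything below rests on assumed inputs.

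**1. Sorting the listed tests**

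- Within-arm: paired t-test; Wilcoxon if signed-rank (the likely reading, since Mann–Whitney is listed separately).
- Between-arm, pre-test ignored: ANOVA or Mann–Whitney on the post-delivery score.
- Between-arm, pre-test used as a repeated outcome: group-by-time term of the repeated-measures ANOVA.
- For categorical data: chi-squared and Fisher's exact tests.
- Between-arm, pre-test as covariate: none.

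**2. Precision**

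Assume equal SDs at both times, pre-post correlation r, 1:1 allocation and large-sample variances. Relative to the unadjusted post-score comparison, the variance of the arm difference is 1 for post-score only, 2(1 − r) for the change score (group-by-time) and 1 − r² for ANCOVA.

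| r | Change score | ANCOVA | Post-score ÷ ANCOVA | Change ÷ ANCOVA |
|---|---|---|---|---|
| 0.3 | 1.40 | 0.91 | 1/0.91 = 1.10 | 1.40/0.91 = 1.54 |
| 0.5 | 1.00 | 0.75 | 1/0.75 = 1.33 | 1.00/0.75 = 1.33 |
| 0.7 | 0.60 | 0.51 | 1/0.51 = 1.96 | 0.60/0.51 = 1.18 |

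The last two columns are the factors by which the number of women must rise to match ANCOVA.

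**3. The same in women per arm**

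Assume a standardised effect of 0.5, two-sided 5% and 80% power. The post-score comparison needs 63 per arm.

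| r | Post-score | Change score | ANCOVA | ANCOVA power at 63 per arm |
|---|---|---|---|---|
| 0.3 | 63 | 88 | 58 | 0.84 |
| 0.5 | 63 | 63 | 48 | 0.90 |
| 0.7 | 63 | 38 | 33 | 0.98 |

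**4. Validity when both arms change naturally**

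This step simulated 4,000 trials per setting, with 63 women per arm, no program effect, and a natural change of 0.3 or 0.5 SD common to both arms. Ranges are over r = 0.3 to 0.7.

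| Result at 5% | 0.3 SD change | 0.5 SD change |
|---|---|---|
| Paired t-test significant in the intervention arm | 53% to 85% | 90% to 99.9% |
| Significant in intervention arm, not in control | 12% to 26% | 0.1% to 9% |

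Over both amounts of change, the between-arm tests kept their level: post-score t-test (two-group ANOVA) 4.7% to 5.7%, group-by-time 4.9% to 5.5%, Mann–Whitney 4.4% to 5.5%.

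A common natural change therefore misleads only through the within-arm tests. The between-arm tests are unaffected, with or without a covariate.

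**The case against.** A reader might infer that, without a covariate, the trial can mistake a natural postpartum change for a program effect. The documents do not support this. The implementation method plans a between-arm comparison after delivery against a randomised, untreated control, and a change common to both arms cancels there. The false-positive rates in step 4 for within-arm testing apply only if the effect is inferred from one arm changing, or from one changing and the other not. The article states no such rule.

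Nor does the article say that the pre-test averages will be tested for significance or used to choose the analysis. It says they will be compared, and a descriptive comparison fits those words.

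The list is also open, since the tests are introduced by the word including, and this is a condensed article. The absence of ANCOVA alone could be left to a fuller plan, and preferring it to valid tests is a matter of efficiency. The loss is moreover capped if the better listed between-arm test is used: at most 33% more women (at r = 0.5), about 10% at r = 0.3 and 18% at r = 0.7.

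All of this stands, and it limits the point. What remains is that the article does state a list, the list joins tests that answer different questions, and none is tied to the objective. The cap also helps only if the better test is chosen in advance, which requires knowing the correlation. ANCOVA does not require that choice: under the step 2 assumptions its large-sample variance never exceeds either alternative.

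**Conclusion.** The point holds as an improvement in clarity and precision. The section should say which between-arm analysis answers the objective, and that analysis should adjust for the pre-test. The size depends on an unstated correlation: over r = 0.3 to 0.7, the post-score comparison needs about 10% to 96% more women than ANCOVA, and the group-by-time test about 54% down to 18% more. These figures assume equal SDs before and after delivery, one post-delivery score, equal allocation and large samples. The direction in favour of ANCOVA does not depend on the value of r within that range.

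The point does not show that the planned between-arm comparison is invalid. It would be serious only if a within-arm result were presented as the effect, which the article neither plans nor rules out.

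**What to change.** In Data analysis, name one primary analysis: a linear model (ANCOVA) of the post-delivery self-efficacy score on allocated arm, with the week-36 pre-test score as covariate, reporting the adjusted mean difference and its 95% confidence interval. If the score is measured at several times after delivery, use a mixed model with the pre-test as covariate.

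State that paired t-test and Wilcoxon results are descriptive and are not evidence of effect, and that the pre-test comparison between arms is reported descriptively. Have the pilot estimate the SD and, as far as its size allows, the correlation between the two scores, and base the sample size on the ANCOVA.

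The cost is a few sentences of rewording. The pre-test is already planned for both arms, and SPSS, the software named in the article, fits the model.

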## Discussion

Adolescent pregnancy can encounter many challenges for the teen mother, family, and health system. Similar to the increase in the global fertility rate in adolescent pregnancy, it is expected that due to human population planning policies in Iran and the provision of childbearing incentives, in the not too distant future, Iran will experience an increasing growth of adolescent pregnancy rates. This matter highlights the urge to develop comprehensive reproductive health care program in order to care for themselves, their infants, and family. Therefore, the current mixed methods study will be conducted as a sequential exploratory approach to provide an interventional program sensitive to the culture of the Iranian society for adolescent mothers in postpartum care. The combination of qualitative and quantitative research methods will result in a more comprehensive view of the self-efficacy needs of teen mothers, and developing programs in postpartum care.

For a teen mother, the simultaneity of two transition periods, i.e. transition to adulthood and transition to the post-partum period, disrupts the acceptance of new roles. The transition from one stage to another is associated with instabilities and requires the acquisition of skills and abilities to adapt to new roles. Teen mother should be able to balance between multiple roles and mood changes. Therefore, a healthy transition requires mental well-being, mastery of roles and good and logical relationships. On the other hand, having a healthy transitional stage depends a lot on the amount of information, the type of attitude and acquired behaviors. Lack of knowledge, information and life skills in managing this situation may threaten the physical and mental health of the mother, family and children and reduce the level of role adaptation. Previous researches show that in adolescent mother, the perceived stress following pregnancy and childbirth is higher than adults; moreover, the perceived stress after childbirth is much higher than pregnancy. Therefore, it seems critical to develop fundamental culturally sensitive community-based interventions in accordance with the biological, cognitive, psycho-social structure of teen mother in order to increase their self-efficacy.

Despite the influence of the adolescent health in many health indicators, investing, and planning in various aspects of their health is often overlooked. Shortage of knowledge of maternal health care providers in the caring of teen mothers along with lack of comprehensive guidelines are the main reasons for neglecting them. By implementing this program, teen mothers can access postpartum services that are appropriate for their age characteristics. Moreover, in this program, in addition to improve the health of mothers, they will also improve their self-efficacy. In the meantime, the conduct of this program is considered as a logical and efficient solution for improving postpartum outcomes, and reduces their medical and treatment costs.

Developing an interventional program that includes mother’s experiences, evidence based practice principles, and health staff opinions in a distinct cultural and social context can supply new direction to lead manager, policymakers, and other health care provider to improve the maternal and child health outcome, as well as quality of postpartum care for teen mothers with considering their age characteristics.

## Data Availability

The data sets will be used and analyzed during the current study are available from the corresponding author upon reasonable request.
